Demographic data • Age • Sex Risk factors and baseline comorbidities • Hypertension • Diabetes mellitus • Hypercholesterolemia • Smoking status • Kidney chronic disease • Previous ACS • Previous Stroke • Heart failure • Atrial fibrillation • Previous PE and DVT • Cancer • Organ transplant • Immunosupresion • Frailty Charlson Comorbidity Index Baseline medication • Anti-hypertensive drugs and cardiovascular medication • Chronic anticoagulation • Oral hypoglycemic agents • Insulin • Proton pump inhibitors • NSAIDs	Symptoms Hospitalization • Length of stay Drugs: • Anti-hypertensive drugs and cardiovascular medication. • Anticoagulation • Antivirals • Immunosuppressive drugs • Vasopressors • ICU admission • Invasive mechanical ventilation Biomarkers • Hemoglobin* • Lymphocytes* • Platelets* • Creatinine** • HscTnI** • NT-proBNP** • D-dimer** • Fibrinogen* • Prothrombin time** In-hospital events: • All-cause death • Cardiovascular death • ACS • Stroke • DVT and PE • Cardiac arrhytmias • Bleeding • Red blood cell transfusion Discharge medication	New SARS-CoV-2 infection Vaccination against SARS-CoV-2 Outcomes • All cause death • Cardiovascular death • ACS • Stroke • Heart failure hospitalization • PE • Cardiac arrhytmias

ACS, acute coronary syndrome; DVT, deep venous thrombosis; Hs-cTnI, high sensitivity cardiac troponin I; NSAIDs, non-steroidal anti-inflammatory drugs; PE, pulmonary embolism.

*Lowest values during hospitalization.

*Highest values during hospitalization.

All the data will be obtained from electronic records (medical history). If deemed necessary, the investigator may check the patient vital status in the social national security database.

Clinical follow-up will be performed at 1-year. The flowchart and study timeline are detailed in **Fig 1**.

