**Fig 1 pone.0255263.g001:**
[figure not shown]
Timeline of the study. Inclusion of the patients will be since March to August 2020. Analysis of the clinical outcomes will be performed in August 2021.

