### Outcomes and definitions

The primary outcome will be:

Cardiovascular mortality at 1-year follow-up, defined according to the Academic Research Consortium-2 [15].

The secondary outcomes will be:

Myocardial infarction: defined according to the Academic Research Consortium-2 [15].Stroke: defined according to the Academic Research Consortium-2 [15].Heart failure hospitalization must be documented in the diagnosis of the hospitalization discharge letter.Pulmonary embolism must be documented with a computed tomography.Cardiac arrhythmias must be documented in the diagnosis of the hospitalization discharge letter. Serious cardiac arrhythmias were defined as: bradycardia requiring intravenous medication or pacemaker, supraventricular tachycardia requiring intravenous medication or cardioversion, or ventricular tachycardia requiring intravenous medication or cardioversion.Major bleeding was defined as a type 3 of the Bleeding Academic Research Consortium (BARC) or higher [16].

All the events will be independently adjudicated by a Clinical Events Committee. The Clinical Event Committee (CEC) consists of cardiologists not participating in the trial. The CEC members will be blinded to PCR COVID of the patient.

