### Statistical analysis plan

We did not estimate a precise sample size, due to lack of literature reports and we aim to get the maximum numbers of patients possible.

Continuous variables will be presented as mean ± standard deviation. Categorical variables will be reported as absolute number and percentage. Differences in proportions will be tested with Chi-square test or Fishers exact test and differences in continuous variables will be tested with a Student’s t-test. Kaplan-Meier method will be used to derive the event rates at follow-up and to plot time-to-event curves. Patients not eligible for 1-year follow-up will be considered at risk until the date of last contact, at which point they will be censored.

To determine the predictors of cardiovascular death, a Cox proportional hazards model will be used together with the Wald test to compare the results between the groups (patients with positive vs. negative RT-PCR for SARS-CoV-2).

All p-values will be two-sided and a value <0.05 will be considered statistically significant. All data will be processed using the Statistical Package for Social Sciences, version 22 (SPSS Inc., Chicago, IL, USA).

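### Last-contact censoring plus a discretionary vital-status check can inflate the 1-year mortality estimate and, if applied unequally, can bias the group comparison in either direction

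*Protocol article*

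**What the plan says.** All references are to the protocol article.

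- **Statistical analysis plan, censoring:** "Patients not eligible for 1-year follow-up will be considered at risk until the date of last contact, at which point they will be censored". The article does not say whether this means patients who entered too late to complete a year, patients lost to follow-up, or both.
- **Statistical analysis plan, methods:** "Kaplan-Meier method will be used to derive the event rates at follow-up and to plot time-to-event curves". The two swab groups are compared with a Cox model and a Wald test.
- **Data capture:** the source is the electronic medical record. In addition, "If deemed necessary, the investigator may check the patient vital status in the social national security database". No trigger, date or common procedure for the two groups is given. The section also says "Clinical follow-up will be performed at 1-year".
- **Fig 1 legend:** "Inclusion of the patients will be since March to August 2020" and "Analysis of the clinical outcomes will be performed in August 2021". The day in August is not stated.
- **Outcomes and definitions:** the primary outcome is cardiovascular mortality at 1 year.

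**The concern.** Kaplan-Meier and Cox estimates are valid only if a patient's censoring time carries no information about the outcome. The two rules together can break that condition. Take two patients last seen at month 3. One dies at month 9, a later check finds the death, and it counts as an event with 9 months at risk. The other is alive, and under the stated rule is censored at month 3. Deaths then keep their full time and survivors lose theirs, so the denominator shrinks and the estimated risk rises.

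The primary comparison is exposed if record contact or use of the check depends on the swab result. The article states blinding for the events committee, but not for the site investigator who decides whether to look up vital status. The committee can adjudicate only the events that sites report.

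The timing is a separate matter. A patient swabbed on 31 August 2020 completes one year on 31 August 2021, so an analysis during August 2021 may come before the end of the 1-year period for the last entrants.

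**Working it through.** The article states no sample size, event rate, loss rate or checking rate, so there is no figure of its own to reproduce. The inputs below are assumptions, shown over a range.

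**1. Bias within one group**

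Inputs (assumed): constant hazard, low risk (2% at one year); a share *f* of patients whose last contact is uniform over the year and unrelated to prognosis; a share *q* of deaths after last contact that is found and counted; everyone else in *f* censored at last contact.

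At time *t* (in years) the risk set is about 1 − *ft*. Counted deaths are proportional to (1 − *ft*) + *qft*. The estimated hazard divided by the true hazard is therefore 1 + *qft*/(1 − *ft*). Integrating from 0 to 1:

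estimated risk / true risk ≈ 1 + *q* × [−ln(1 − *f*)/*f* − 1]

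| *f* | −ln(1 − *f*)/*f* | *q* = 1 | *q* = 0.5 | *q* = 0 |
|---|---|---|---|---|
| 20% | 0.2231/0.2 = 1.12 | 1.12 | 1.06 | 1.00 |
| 40% | 0.5108/0.4 = 1.28 | 1.28 | 1.14 | 1.00 |
| 60% | 0.9163/0.6 = 1.53 | 1.53 | 1.26 | 1.00 |

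A simulation of 1,000,000 patients at a true 2% agrees. With *f* = 30% and 50% it gives 2.38% and 2.78% for *q* = 1 (formula: 2 × 1.189 = 2.38 and 2 × 1.386 = 2.77), and 2.18% and 2.39% for *q* = 0.5. The last column of the table shows that last-contact censoring alone causes no bias when contact is unrelated to prognosis. The mixture of two rules causes it.

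**2. Bias between groups**

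True ratio 1.00, true risk 5%, 1,000,000 patients per group. The event rate per person-time, a proxy for the Cox hazard ratio, is inflated in each group by about 1 + *q*(*f*/2)/(1 − *f*/2).

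| *f* positive / negative | *q* positive / negative | Formula | Simulated ratio |
|---|---|---|---|
| 30% / 30% | 1 / 1 | 1.00 | 1.00 |
| 10% / 50% | 1 / 1 | 0.75/0.95 = 0.79 | 0.81 |
| 10% / 50% | 0.5 / 0.5 | 1.026/1.167 = 0.88 | 0.89 |
| 30% / 30% | 1 / 0.5 | 1.176/1.088 = 1.08 | 1.07 |
| 30% / 30% | 1 / 0 | 1.176/1.000 = 1.18 | 1.17 |
| 10% / 50% | 0 / 0 | 1.00 | 1.01 |

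An equal process gives no bias in the ratio. An unequal one can push it either way.

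**3. Timing**

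Inclusion from 1 March to 31 August 2020 is 31 + 30 + 31 + 30 + 31 + 31 = 184 days. The inclusion days with under 365 days of follow-up are:

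- cut on 1 August 2021: 2 to 31 August, 30/184 = 16.3%;
- cut on 15 August 2021: 16 to 31 August, 16/184 = 8.7%;
- cut on 31 August 2021: 0/184 = 0%.

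These are shares of days. They are shares of patients only if accrual was uniform.

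**4. After the change**

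If every patient's status is known to a common date (*f* = 0), the simulation returns 4.98% to 5.03% for a true 5%.

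**The case against.** The censoring sentence names only patients not eligible for 1-year follow-up. A natural reading is that it covers late entrants alone, since 1-year follow-up is planned for everyone. A vital-status lookup also returns alive as well as dead, and a survivor found alive could be credited with time up to the lookup. If sites did that for every patient without a 1-year contact, the asymmetry would disappear. Independent monitors also audit follow-up and events in a random 10% of patients.

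Part of this stands. The rule may reach few patients, and the bias needs later deaths to be counted while comparable survivors keep the earlier date. But the eligibility phrase is undefined, the only censoring date the article gives is last contact, and no sentence credits a checked survivor with later time. Even if only late entrants are meant, they are censored at last contact and not at the data cut. A 10% audit does not change the rule.

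A reader might infer more, and three such readings are not supported:

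- *Censoring is informative by construction.* It is not: with *q* = 0 and contact unrelated to prognosis the estimate is unbiased.
- *Follow-up differs between the groups.* Symptom-free controls might have fewer hospital contacts, but the article gives no contact, loss or checking rates by group. A contrast of 20% against 60% without 1-year contact would put the ratio of Kaplan-Meier risks out by 1.53/1.12 = 1.37 with complete death capture, but by 1.26/1.06 = 1.19 with half capture and not at all with none. Those fractions are assumed.
- *The August 2021 analysis makes censoring informative or leaves no time for adjudication.* Truncation by entry date is administrative, and adjudication could run as events arrive.

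**Conclusion.** The point holds as a risk that the stated rules leave open, not as a demonstrated bias. Censoring at last contact together with a discretionary vital-status check can inflate the 1-year cardiovascular mortality estimate. On the assumptions above, the inflation is about 12% to 53% if all later deaths are found, 6% to 26% if half are, and nil if none are. The calculation treats each later death as a primary event.

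The group comparison is unaffected if contact and checking are the same in both groups. If they differ, the simulated ratio under a true 1.00 ran from 0.81 to 1.17 in the cases tried, so even the direction cannot be predicted. Nothing in the article ensures equal handling.

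The analysis date is a smaller, separate weakness. Depending on the cut, 0% to 16% of inclusion days lack a full year.

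**What to change.** - Check vital status for every patient in both groups at one common date after 31 August 2021, by the same procedure whatever the swab result.
- For mortality, censor survivors at day 365 or at that common date, not at last contact.
- Run the 1-year analysis after that date.
- For non-fatal events, keep last record contact as the censoring date. A vital-status check cannot show that an infarction, stroke or admission did not occur, so carrying these patients forward as event-free would be unsound.
- Define who is not eligible for 1-year follow-up, and report completeness of follow-up by group.

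The cost is one systematic query through database access that the plan already has, and a delay of some weeks. No new patients are needed.

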**Study and design:**

This is a multicenter, observational, retrospective registry to be conducted at 17 centers in Spain and Italy (ClinicalTrials.gov number: NCT04359927). Consecutive patients older than 18 years, who underwent a real-time reverse transcriptase-polymerase chain reaction (RT-PCR) for SARS-CoV2 in the participating institutions, will be included since March 2020, to August 2020. Patients will be classified into two groups, according to the results of the RT-PCR: COVID-19 positive or negative. The primary outcome will be cardiovascular mortality at 1 year. The secondary outcomes will be acute myocardial infarction, stroke, heart failure hospitalization, pulmonary embolism, and serious cardiac arrhythmias, at 1 year. Outcomes will be compared between the two groups. Events will be adjudicated by an independent clinical event committee.

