## Methods

### Study design

It is a multicenter, observational, retrospective registry to be conducted at 17 centers in Spain and Italy. This study is an investigator-initiated registry, and the promoter is the Fundació Clínic per a la Recerca Biomédica. **Table 1** shows the list of enrolling centers and their principal investigators. The detailed list of the study staff is in the **S1 File**.

**Table 1 pone.0255263.t001:** Centers and investigators.

Centers	Investigators
Hospital Universitari Clínic de Barcelona	[name]
Hospital Universitari Sagrat Cor	[name]
Hospital Universitari de Bellvitge	[name] [name]
Hospital Marqués de Valdecilla	[name] [name]
Hospital Universitario Juan Ramón Jiménez	[name] [name], [name] [name]
Hospital Universitario La Princesa	[name]
Hospital Universitari Vall d’Hebron	[name] [name]
Hospital Clínico Universitario de Valladolid	[name] [name]
Hospital Universitario de León	[name]
Hospital Universitario de Vigo	[name] [name]
Hospital Universitario Clínico San Carlos	[name]
Istituto Clinico Sant’Ambrogio	[name]
Azienda Ospedaliero-Universitaria di Ferrara	[name]
Hospital de Tortosa Verge de la Cinta	[name]
Ospedale Bolognini di Seriate	[name]
Hospital Universitari Arnau de Vilanova	[name]
Hospital Universitari Joan XXIII	[name]

The Registry does not test clinical interventions, and individual patient care is entirely at the discretion of treating clinicians.

This study adhered to the principles outlined in the Declaration of Helsinki. Approval was given by the “Comité de Ética de la Investigación con medicamentos del Hospital Clínic de Barcelona” (Ethics Committee for Drug Research of the Hospital Clínic of Barcelona) with the registry HCB/2020/0457, on April 16, 2020. Given the registry’s anonymous characteristics and the health alarm situation generated by the COVID-19 pandemic, written informed consent was waived.

The study is registered at ClinicalTrials.gov (NCT number: NCT04359927).

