### Patient selection

Inclusion criteria are:

At least 18 years of age.Patient who underwent a nasopharyngeal swab for real-time reverse transcriptase-polymerase chain reaction (RT-PCR) for SARS-CoV2 between March 2020 and August 2020.

Exclusion criteria are:

Those with terminal diseases and a life expectancy <1 year before the diagnosis will be excluded.

Patients will be classified into two groups: patients with confirmed COVID-19 (positive RT-PCRT for SARS-CoV-2) and patients without COVID-19 (negative RT-PCR for SARS-CoV2, and absence of absence of suspicious symptoms).

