## Discussion

In this multicenter, observational, retrospective registry, we aim of investigate the long-term cardiovascular implications of COVID-19. Currently is known that the presence of myocardial injury, vascular dysfunction and thrombosis in patients with COVID-19 have an important role in the short-term prognosis in these patients [9]. Previous experience with the severe acute respiratory syndrome coronavirus-1 (SARS-CoV-1) emerged in 2002, suggests that both the underlying disease and its treatment could be associated with a worse cardiovascular prognosis. In a study of 25 survivors of SARS-CoV-1, at 12 years of follow-up, altered lipid metabolism was found [17]. Similarly, viral diseases such as influenza A are associated with increased cardiovascular mortality after infection [18].

The focus of this registry will be on the cardiovascular outcomes, providing data not only about cardiac ischemic events but also arrhythmias, cerebrovascular events and heart failure. It should be highlighted that our findings will be applicable to any COVID19 patient, regardless of the severity of the disease, as we will be including a consecutive population of patients with COVID-19 infection. Confirmed cases will be evaluated and compared with those patients who did not have COVID-19 infection. This approach will offer a greater security at the moment of assessing study’s findings. This control group will help to minimize bias that would arise if only COVID-19 patients were independently analyzed. Cox regression will help to distinguish the independent predictors for mortality among the patients of the study. However, considering that a proportion of the SARS-CoV-2 infections can be asymptomatic, there can be a degree of bias if the control patients (non-COVID-19 group) become infected but exhibit an asymptomatic disease during follow-up. Nevertheless, potential patients fulfilling these characteristics can represent a minimal part of the sample size.

It is important to mention as strength of the study, that the events will be adjudicated by an independent committee blinded to the patients’ treatment allocation and trial results. This will guarantee a better evaluation of the study events.

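### The RT-PCR group comparison is merged with a predictor search for cardiovascular death, and every method stated for the secondary outcomes is unadjusted

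*Protocol article*

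**What the plan says.** The Study design section describes the study this way: "It is a multicenter, observational, retrospective registry to be conducted at 17 centers in Spain and Italy". Patients are grouped by swab result. Under Patient selection, controls are defined by "negative RT-PCR for SARS-CoV2, and absence of absence of suspicious symptoms". That wording is garbled, but it appears to require controls to be free of suspicious symptoms. Cases need only a positive swab.

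The abstract states the aim of the comparison for primary and secondary outcomes together: "Outcomes will be compared between the two groups". The primary outcome is cardiovascular mortality at one year. Outcomes and definitions lists the secondary outcomes as myocardial infarction, stroke, heart failure hospitalization, pulmonary embolism, arrhythmias and major bleeding.

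The Statistical analysis plan section gives these methods:

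- "Differences in proportions will be tested with Chi-square test or Fishers exact test", with a t-test for continuous variables.
- Kaplan-Meier event rates and curves.
- One regression: "To determine the predictors of cardiovascular death, a Cox proportional hazards model will be used together with the Wald test". The same sentence assigns this model the comparison of RT-PCR positive with negative patients: "a Cox proportional hazards model will be used together with the Wald test to compare the results between the groups".

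The Discussion adds that Cox regression will single out independent predictors of mortality. Of the comparator it says: "This control group will help to minimize bias that would arise if only COVID-19 patients were independently analyzed".

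**The concern.** Estimating the effect of an exposure and searching for predictors are different tasks with different rules for covariates. An exposure model keeps the exposure in, adjusts for a fixed set of variables that precede it, and leaves out its consequences. A predictor search keeps whatever predicts. It may drop a confounder that is weak in the sample, and it may admit a strong marker of severity that lies on the path from infection to death. The plan gives one model both tasks, and the task it names first is the predictor search.

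The secondary outcomes have a different problem. The article promises a group comparison for them but names no adjusted method. The groups appear to differ by definition in symptoms, and they were recruited over six months at 17 centres in two countries. A crude difference between them may reflect who was swabbed rather than the infection. What is at stake is whether the registry can answer its own question, the cardiovascular consequences of COVID-19.

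**Working it through.** **Plan's own figure.** There is none to reproduce. The article states no sample size, event count, power or effect size, only a two-sided 0.05 level (critical z = 1.96).

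**Step 1. Match outcomes to stated methods.**

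| Outcome | Methods stated | Adjusted? |
|---|---|---|
| Cardiovascular death | Kaplan-Meier; Cox model with Wald test | Implied by the Discussion; covariates not fixed in the article |
| MI, stroke, heart failure hospitalization, PE, arrhythmias, major bleeding | Kaplan-Meier; chi-square or Fisher, if that sentence covers outcomes | No |

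If the chi-square sentence covers baseline description only, the secondary outcomes are left with Kaplan-Meier and no stated test between groups. Neither reading gives them an adjusted comparison.

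**Step 2. What could enter the Cox model.** Table 2 has a baseline column (age, sex, risk factors, cardiovascular history, Charlson index and others) and an acute-phase column (ICU admission, invasive ventilation, troponin, D-dimer and others). The analysis section does not limit the model to the baseline column. Read as a predictor search, it leaves both columns open. Acute-phase variables are legitimate predictors of death, but adjusting for them would remove part of the effect of infection.

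**Step 3. How much an unadjusted confounder could matter.** Every input here is an assumption, and there is no true effect of infection. Take one binary confounder with prevalence p1 in cases and p0 in controls, and rate ratio RR for the outcome:

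spurious ratio = [p1(RR − 1) + 1] / [p0(RR − 1) + 1]

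- 40% vs 30%, RR = 2: 1.40/1.30 = 1.08
- 40% vs 30%, RR = 5: 2.6/2.2 = 1.18
- 50% vs 30%, RR = 2: 1.50/1.30 = 1.15
- 50% vs 30%, RR = 5: 3.0/2.2 = 1.36
- Reversed imbalance: from 0.93 (30% vs 40%, RR = 2) to 0.73 (30% vs 50%, RR = 5)

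With equal groups and D events, the crude test statistic is shifted by m = √(D × 0.25) × ln(ratio). For D = 100 and the 1.36 case, m = 5 × 0.310 = 1.55. The nominal 5% test then rejects with probability P(Z > 1.96 − 1.55) + P(Z < −1.96 − 1.55) = 34.1%. For the 1.08 case it rejects 6.6% of the time. With 200 events the two figures are 59.2% and 8.2%.

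**Step 4. The same point with age.** Spurious HR = (HR per decade)^(age difference/10). A 5-year difference with the hazard doubling per decade gives 2.0^0.5 = 1.41. The range runs from 1.5^0.3 = 1.13 (3 years, 1.5 per decade) to 2.5^1.0 = 2.5 (10 years, 2.5 per decade). The article gives neither the age difference nor the gradient. These figures apply only to a comparison in which age is not adjusted for.

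**The case against.** A reader might infer that confounding by age, comorbidity and centre remains in the main result. The document does not support that. The main result is cardiovascular mortality, the one outcome with a Cox model, and the Discussion's reference to independent predictors implies that this model has several covariates. Age and comorbidity may well be among them. This objection stands, and it limits the point on the primary outcome to what the predictor framing leaves open.

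This is also a condensed article. A covariate list, a selection rule and the handling of centre commonly sit in a fuller plan that is not shown. Their absence is not a finding, and silence about centre is not a decision to ignore it. That stands too. It does not cover the stated sentence that gives one model two aims, or the restriction of the only regression to cardiovascular death.

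The chi-square sentence follows directly on the summary statistics and may concern baseline description. It would be wrong to say the secondary outcomes have only chi-square tests, since Kaplan-Meier is also stated. But Kaplan-Meier as stated is unadjusted, so this changes the description and not the conclusion.

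The Discussion's sentence on the control group is a comparative one: having controls is better than having none. That is fair, and it does not claim that controls remove confounding. Still, the only bias the Discussion goes on to name for the comparison is asymptomatic infection among controls. Confounding is not mentioned.

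**Conclusion.** The concern holds in two parts. For the primary outcome, the exposure contrast is merged with a predictor search, so the adjusted estimate depends on predictor selection, and no stated rule excludes consequences of infection. For the secondary outcomes, every stated method is unadjusted although a comparison of non-randomised groups is promised. A crude difference there cannot be attributed to COVID-19.

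The size and direction of the bias cannot be derived from the document. The spurious ratios of 1.08 to 1.36 (or 0.93 to 0.73) and the hazard ratio of 1.41 are illustrations under assumed inputs for an unadjusted comparison. They are not estimates for this registry and should not be read as the bias in its primary result. The point is worth correcting because the repair is cheap and bears directly on the registry's question.

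**What to change.** Separate the two aims in the analysis section.

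1. **Exposure effect.** For cardiovascular death and for each secondary outcome, fit a Cox model with RT-PCR group forced in. Adjust for a fixed set of confounders from the baseline column of Table 2: at least age, sex, the main cardiovascular risk factors and history, and comorbidity. Account for centre by stratification or clustering. Admit no acute-phase variable. Where events are few, use a propensity score or a reduced or penalised covariate set.
2. **Predictor model.** Report it separately and label it exploratory. Acute-phase variables may be used here.

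State also whether the chi-square and t-tests are for baseline description only. Finer choices, such as splines for age, adjustment for calendar month of the swab, or overlap weighting as a sensitivity analysis, are optional. Table 2 does not list the month of swab, so its availability would need checking in the case report form.

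The cost is revised wording, modest extra analysis and somewhat wider intervals when events are few. The core covariates are already collected.
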